**Ministry of Health**

**Chikankata health services**

# ABbreviations

| **ACTs** | **Artemisinin-based combination therapies** |
| --- | --- |
| **AIDS** | **Acquired Immunodeficiency Syndrome** |
| **ALRI** | **Acute Lower Respiratory tract Infections** |
| **BUSPH** | **Boston University School of Public Health** |
| **CER** | **Cost-effectiveness Ratio** |
| **CHS** | **Chikankata Health services** |
| **CHW** | **Community Health Worker** |
| **CIHD** | **Center for International Health and Development** |
| **CPTs** | **Care and Prevention Teams** |
| **CRFs** | **Case Report Forms** |
| **DC** | **Data Collector** |
| **DHMT** | **District Health Management Team** |
| **DS** | **Data Supervisor** |
| **DSMB** | **Data Safety and Monitoring Board** |
| **GEE** | **Generalizing Estimating Equation** |
| **HCC** | **Health Center Committee** |
| **HIV** | **Human Immunodeficiency Virus** |
| **ICC** | **Intra-cluster Correlation** |
| **IMCI** | **Integrated Management of Childhood Illness** |
| **MOH** | **Ministry of Health** |
| **NGO** | **Non-governmental Organization** |
| **NHC** | **Neighborhood Health Committee** |
| **NMCC** | **National Malaria Control Center** |
| **OPD** | **Outpatient Department** |
| **PHC** | **Primary Health Care** |
| **RDTs** | **Rapid diagnostic tests** |
| **RHC** | **Rural Health Center** |
| **ZIMMAPS** | **Zambia Integrated Management of Malaria and Pneumonia Study** |

# 1. Study Synopsis

# The Zambia Integrated Management of Malaria and Pneumonia Study (ZIMMAPS) will be a cluster randomized controlled trial to demonstrate the effectiveness and feasibility of community-based management of pneumonia and malaria by community health workers (CHWs) in a rural district of Zambia. The CHWs will be aided by the use of rapid diagnostic tests (RDTs) to differentiate between fever due to malaria and fever due to other causes, especially pneumonia, with the overarching goal of enhancing the capacity of CHWs to provide early, effective and appropriate treatment to children under five in areas of particularly poor access to facility based health care.

The study will be conducted in the Chikankata Health Services (CHS) area, which covers parts of Mazabuka and Siavonga Districts of the Southern Province of Zambia. It will be a collaborative venture between the Center for International Health and Development (CIHD) of Boston University School of Public Health (BUSPH), Mazabuka and Siavonga District Health Managements (DHMTs), the Ministry of Health (MOH) and CHS, a non-governmental organization (NGO).

Existing supported CHWs in the study area will be trained in the assessment and classification of children between six months and five years of age presenting with fever and/or cough/difficult breathing. In the intervention arm, CHWs will be supplied with RDTs, Coartem® and amoxicillin. The intervention CHWs will be trained to use RDTs in patients with reported fever and provide those with a positive result with Coartem; and patients suspected of pneumonia (based on fast breathing) will be treated with amoxicillin as per the standard of care at health facilities and monitored. In the control group, no RDT will be performed. The CHWs will be supplied with Coartem to treat malaria/febrile illness as per the integrated management of childhood illnesses (IMCI) guidelines and patients suspected of pneumonia will be referred to the health facility for treatment as per the current practice. Data collectors will routinely visit CHWs to collect data on their consultations and follow-up patients treated by CHWs in their homes..

# 2. BACKGROUND AND RATIONALE

Pneumonia and malaria are the two leading causes of morbidity and mortality among children under five in sub-Saharan Africa. Pneumonia accounts for nearly one-fifth of childhood deaths worldwide, with approximately 2 million children under five dying each year. The majority of deaths occur in Africa and Southeast Asia.1 Childhood malaria, and in particular *P. falciparum* malaria, remains a major public health problem, with an estimated one million children dying each year of malaria and its complications.2,3 Recent estimates of the global distribution of clinical episodes of *P. falciparum* malaria suggest that the burden of malaria in Africa may even be grossly underestimated.4

Malaria is the most significant health problem in Zambia accounting for, by far, the greatest number of pediatric outpatient consultations and hospital admissions. The National Malaria Control Center (NMCC) estimates that malaria is responsible for nearly 4.3 million clinical cases and an estimated 50,000 deaths per year5.

# A large proportion of these deaths could be prevented through early, appropriate and low-cost treatment of sick children. The IMCI algorithm represents a notable attempt to extend these basic health care services to sick children. IMCI was designed to be implemented in primary health care clinics by health workers who only have a rudimentary level of education or medical training.

Improvements in care at health facilities through IMCI and other initiatives are necessary, but have been found not to be sufficient6. Children from the poorest families are significantly less likely to be brought to health facilities, and may receive lower quality care once they arrive7,8. Even where impressive gains are made in the quality of care in health facilities, the level of care seeking from these same facilities remains suboptimal 9,10 and these services are geographically not accessible to the majority of the children who need them. The health needs of large numbers of sick children in developing countries are provided through the informal sector (which may include CHWs and drug sellers) or traditional healers11, rather than through primary health care facilities where IMCI protocols might be in use.

Since access to health services is limited in Sub-Saharan Africa and a majority of African children die at home12, new and innovative approaches to reducing childhood mortality will require interventions implemented at the community level.

Consequently, child survival programs have placed increasing importance on early and appropriate treatment of malaria and pneumonia within the community, and preferably within the child’s own home. Two recent studies from Bangladesh and Nepal demonstrated the feasibility and effectiveness of training CHWs to manage acute lower respiratory tract infections (ALRI)13,14. In both cases, this model of care led to significant reductions in childhood mortality, and, importantly, was well accepted by community members. A meta-analysis of studies from eight Asian and one African nation (Tanzania) found that community-based management of pneumonia reduced mortality by 36% among infants and children.15 Similarly, a number of studies have shown that CHWs can be trained to provide effective malaria case management in the community16,17. In a large community-based, cluster randomized trial in northern Ethiopia, CHWs were trained to identify malaria on clinical grounds and to administer chloroquine in the field. This approach generated an impressive 40% reduction in all-cause mortality, with the greatest reduction due to reduced malaria deaths.15

# At present most malaria illnesses are diagnosed on highly non-specific clinical grounds alone, without the benefit of diagnostic tools. Consequently, antimalarial drugs are administered presumptively to children with history of fever. This practice leads to substantial over treatment and may accelerate the evolution of anti malarial drug resistance, as well as wasting scarce resources and delaying diagnosis and treatment of other febrile illnesses especially pneumonia. With Zambia’s recent decision to replace sulfadoxine-pyrimethamine (Fansidar®) with artemether-lumefantrine (Coartem®) for use by CHWs, the potentially harmful effects of presumptive use of this drug might become even more pronounced.

In an attempt to provide an effective alternative to the traditional method of malaria testing, malaria RDTs have been developed. While RDTs can be effective in clinical settings when used by trained personnel, they also have great potential in rural areas with limited access to health facilities and health professionals18. RDT use by CHWs at the village level presents a tremendous opportunity to improve malaria diagnosis and treatment. It should lead to making a definitive diagnosis in a much greater proportion of cases and significant cost savings by avoiding unnecessary use of expensive artemisinin-based combination therapies (ACTs) and thus may help reduce the development of drug resistance. Given the high cost of ACTs, the Zambia MOH has adopted strategies to improve malaria diagnostics (microscopy and the use of RDTs to rationalize the use of ACTs in peripheral clinics. The Quality Assurance Project in partnership with the Special Programme for Research and Training in Tropical Diseases, the World Health Organization Regional Offices for the Western Pacific and Africa (AFRO) and the Zambian MOH has developed and tested an RDT job aid to enable CHWs safely and effectively use RDTs. The Zambian MOH is currently discussing the mechanism of how to deploy RDTs to improve malaria diagnosis at the community level.

# A number of global health organizations, including the World Health Organization, have strongly advocated the use of CHWs to deliver basic health care in the community and to facilitate referral to primary health facilities. The symptoms of malaria and pneumonia overlap to a great extent, and therefore to adequately treat the sick child, these community strategies need to address the malaria-pneumonia symptom overlap and manage both conditions 19. However, there are limited studies that have evaluated CHWs managing both ALRI and malaria; and no study has thus far carefully evaluated CHWs delivering artemisinin-based combination therapy. The potential benefit of RDT in improving malaria diagnosis before treating with ACTs by CHWs also needs to be proven.

The purpose of this project is to demonstrate the effectiveness and feasibility of training CHWs and supplying them with RDTs, Coartem and amoxicillin to treat both pneumonia and malaria at the community level, with the overarching goal of enhancing the capacity of CHWs to provide early, effective and appropriate treatment to children under five in areas of particularly poor access to facility based health care. We decided to work with CHWs because the Zambia MOH recognizes the role of CHWs in providing cost effective and quality health care as close to the family as possible and is committed to supporting and strengthening the implementation of community based health care. The MOH with support from other partners has developed a reference manual for CHWs. This manual is being used by DHMTs, which in partnership with NGOs are running CHW programs in many parts of the country. The project will be conducted in close partnership between CIHD, the Zambian Ministry of Health and the Salvation Army World Service Office, a NGO working in Southern Zambia. We believe that the dual disease management model will prove feasible and effective, and offer a new model of care that will be highly relevant in Zambia and throughout sub-Saharan Africa.

We do recognize the challenges inherent in wide-scale use of CHW programs, which may include maintaining and ensuring high level of performance, development of less complex and culturally appropriate job aids20, retention, motivation and incentives, health systems support (in the area of provision of drugs and supplies, supervision and referrals) and community support. These issues will be addressed in designing the study. We hope that the study will provide useful lessons for scaling up this approach.

# 3. OBJECTIVES AND OUTCOME VARIABLES

**3.1 Main Objective**

- To demonstrate the effectiveness and feasibility of integrated management of fever (malaria and pneumonia) at the community level using CHWs with the aid of RDTs.

**3.2.1 Primary Objectives**

- To determine whether the integrated management of malaria and pneumonia by CHWs at the community level increases the proportion of children under five years old who receive early and appropriate treatment for pneumonia as compared to children referred to health facility.
- To determine the extent, to which the use of RDTs by CHWs reduces the use of Coartem® in the management of children with acute fever, compared with management based on clinical criteria only.

**3.2.2 Primary Hypotheses**

- The proportion of children with fast breathing who receive early and appropriate treatment for pneumonia will be increased by at least 20% among CHWs trained to treat both malaria and pneumonia.
- The proportion of children presenting with fever who receive Coartem® will be reduced by at least 20% among CHWs trained in the use of RDTs.

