# 4.2 Study design

The study will be a cluster-randomized controlled trial. A study cluster will be defined as the catchment area of a community health post. CHWs work from a community health post with well defined catchment area and population within a health facility catchment area and are supervised by the staff of the health facility. The clusters (community health post catchment area) will be matched in pairs according to the health facility catchment area they belong to, the distance from the health facility and the population size. Randomization will then be done from among the matched clusters to select the intervention and the control arms. CHWs in both the intervention and control arms will receive training in the assessment and classification of children presenting with fever and/or cough/difficult breathing. The CHWs in the intervention arm will be supplied with RDTs, Coartem® and amoxicillin. The intervention CHWs will be trained to use RDTs in patients with reported fever and provide those with a positive result with Coartem while patients suspected of pneumonia (based on fast breathing) will be treated with amoxicillin as per the standard of care at health facilities and monitored. Those with negative RDT result will be treated with antipyretic and asked to return if they do not get better after 48 hours or condition deteriorates. In the control group, no RDT will be performed. The CHWs will be supplied with Coartem to treat malaria/febrile illness as per the IMCI guidelines and patients suspected of pneumonia will be referred to the health facility for treatment as per the current practice. The supply of the drugs and RDTs will come through the normal MOH sources. The study will utilize specialized field workers (data collectors and data supervisors) to visit CHWs to collect data on their consultations and follow-up children treated by CHWs. Consent will be sought from caregivers to allow us collect data by which to assess the effectiveness of the intervention. Caregivers in both the intervention and control arms are not obliged to receive care from the CHWs. They are free to go to any of the health facilities in the study area instead of a CHW. The study will collaborate with the MOH and the DHMTs to ensure that the health facilities in the study area have RDTs, Coartem and amoxicillin.

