**4.3 Sample Size**

This study will be a cluster randomized trial at the level of the community health post. As a result, we need to take the intracluster correlation within individuals receiving treatment at each community health post in both the calculation of sample size and data analysis.

The two primary study hypotheses were stated earlier: one for the treatment of children with fast breathing and one for the treatment of children with fever. We will calculate a sample size for each of the study hypothesis

There are 43 community health posts in the study area. This will be a two-arm study so we will have 21 community health posts available for each arm with a 1:1 allocation. All of the calculations are made using the assumption of 80% power to show differences and a two side alpha of 0.05.

The sample size for a cluster randomized trial is based upon the intracluster coefficient (ICC). As we do not have accurate information on the expected ICC for the outcomes in this study, the sample size is presented as a series of sample size calculations given a range of the ICC values which we would expect to see.

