**Treatment of children presenting with fever**

Currently 100% of children seen with fever should receive Coartem treatment. We hypothesize that with the use of an RDT, the proportion of children receiving Coartem treatment would be reduced to 80%.

**Sample size necessary to detect a 20% decrease of children not receiving Coartem for various ICCs**.

| Intracluster coefficient | Total Clusters | Sample per cluster | Total sample size |
| --- | --- | --- | --- |
| 0.05 | 38 | 2 | 76 |
| 0.07 | 40 | 2 | 80 |
| 0.09 | 42 | 2 | 84 |
| 0.11 | 34 | 3 | 102 |
| 0.13 | 36 | 3 | 108 |
| 0.15 | 36 | 4 | 144 |
| 0.17 | 36 | 5 | 180 |
| 0.19 | 38 | 6 | 228 |
| 0.21 | 38 | 12 | 456 |
| 0.23 | 40 | 33 | 1320 |
| 0.25 | 46 | 36 | 1656 |

At the largest ICC of 0.25, 46 clusters enrolling 36 subjects each for a total of 1656 subjects would be necessary to show a difference between the intervention and control arms. Since we do not have 46 clusters, and no feasible increase in subjects per arm will allow us to reduce the total clusters to 42, we would be underpowered with an ICC of 0.25. However, we would be able to meet the study enrollment needs at every other ICC. At the smallest ICC of 0.05, the total sample size would be only 76 subjects being recruited from 38 clusters with 2 subjects per cluster. Therefore, within these likely ranges of ICC we would need to enroll between 76 and 1320 subjects. Following the logic above we would enroll 1320 subjects. We anticipate a drop out rate of 15%; hence we will increase our sample size to 1518 children with fever.

All of the 49 CHWs supported by CHS will be used.

20 households per cluster will be selected through multi-stage sampling. 420 caregivers will therefore be interviewed. Since the household survey will be repeated at the end of the intervention, a total of 840 caregivers will be interviewed.

The total sample size for the study will be 2931 (524 + 1518 + 840 + 49)

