**6.0 Statistical Analyses**

# 6.1 Primary end-points comparison

There are two primary endpoints for the study depending upon whether a child has fever or fast breathing. For children with fever the primary outcome is appropriate treatment with Coartem® and for children with fast breathing the primary outcome is early and appropriate treatment. For each primary outcome, crude proportions in the two groups will be compared using the Mantel-Haenszel chi-square test with clusters as strata to account for the cluster randomization. Crude data will be presented as cluster adjusted odds ratios and 95% confidence intervals. Inferences about treatment effects will be made at the level of the individual not at the level of the cluster. Analyses will be based on an intent-to-treat basis.

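### Both primary hypotheses claim a change of at least 20%, but the planned tests can only show some change, and the planned odds ratio cannot measure the Coartem reduction

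*Protocol*

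**What the plan says.** Section 3.2.2 gives two primary hypotheses, each with a minimum effect. For Coartem: "The proportion of children presenting with fever who receive Coartem® will be reduced by at least 20% among CHWs trained in the use of RDTs". For fast breathing, the proportion treated early and appropriately "will be increased by at least 20% among CHWs trained to treat both malaria and pneumonia".

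Section 4.3 fixes the scale by example: 50% to 70% for fast breathing and 100% to 80% for fever. It sets an "assumption of 80% power to show differences and a two side alpha of 0.05". On the fever control rate it says: "Currently 100% of children seen with fever should receive Coartem treatment".

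The primary objectives in section 3.2.1 carry no threshold. The Coartem objective is one of estimation: "To determine the extent, to which the use of RDTs by CHWs reduces the use of Coartem".

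Section 6.1 plans a Mantel-Haenszel chi-square test of the crude proportions and then: "Crude data will be presented as cluster adjusted odds ratios and 95% confidence intervals". The multivariable analysis is a GEE model on the log-odds scale, again summarised by odds ratios. The protocol gives no 20-point margin, no rule for reading a confidence limit against 20 points, and no risk difference or ratio of proportions with an interval.

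**The concern.** A hypothesis that the change is at least 20 points has, as its complement, every change smaller than 20 points. The planned tests put their null at zero. Rejecting zero leaves a change of 5, 10 or 15 points open, and each of those contradicts section 3.2.2 as written.

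The effect measure does not close the gap. An odds ratio can be converted to points only with a baseline rate, and at the protocol's own fever baseline it cannot be converted at all. Section 9.5 expects the results to bear on national policy, where the size of the Coartem saving is the useful quantity. The protocol would then report a p-value and an odds ratio beside a hypothesis that neither of them addresses.

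**Working it through.** **Inputs (section 4.3).** Fever: control 100%, intervention 80%, 40 clusters of 33 (1320 children) at the tabulated coefficient 0.23. Fast breathing: 50% and 70%, 38 clusters of 12 (456 children) at 0.25. Two-sided 5%, 80% power. Clusters are pair-matched (section 4.2).

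**1. Reproducing the sample sizes.** The pair-matched Hayes-Bennett formula, with the tabulated coefficient entered as a between-cluster coefficient of variation k, reproduces every row of both tables:

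c per arm = 2 + (1.96 + 0.84)² × [p0(1−p0)/m + p1(1−p1)/m + k²(p0² + p1²)] / (p0 − p1)²

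- Fever: 0 + 0.16/33 + 0.0529 × 1.64 = 0.0916. Then 2 + 7.849 × 0.0916/0.04 = 19.97, so 20 per arm, 40 clusters, 1320 children.
- Fast breathing: 0.25/12 + 0.21/12 + 0.0625 × 0.74 = 0.0846. Then 2 + 7.849 × 0.0846/0.04 = 18.60, so 19 per arm, 38 clusters, 456 children.

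The null in this formula is zero and 20 points is the alternative. If the null were a 20-point change, the denominator at the planned rates would be (0.20 − 0.20)² = 0 and no sample size would suffice. The sizing therefore treats 20 points as a planning difference, not as something to be proved.

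**2. The odds ratio for Coartem.** Take the endpoint as section 3.4 defines it (receipt of Coartem). At 100% control use the control odds are 1/0, which is infinite.

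- 20-point fall: intervention odds 0.80/0.20 = 4, so the odds ratio is 0.
- 5-point fall: intervention odds 0.95/0.05 = 19, so the odds ratio is again 0.

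Inverted, both are infinite. The log odds ratio that the GEE is to estimate is not finite, and the value does not distinguish a small fall from a large one.

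For fast breathing the design odds ratio is (0.7/0.3)/(0.5/0.5) = 2.33. From an illustrative 80% baseline (my assumption) the same ratio gives odds 4 × 2.33 = 9.33, or 90.3%, about 10 points. It can be read as 20 points only if the 50% baseline holds.

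**3. Chance of rejecting no difference when the true fall is under 20 points.** The tabulated coefficient can be read as k or as an ICC. For the ICC reading I used the effective sample per arm n = 20 × 33/(1 + 32 × ICC) and

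power = Φ{[d − 1.96√(2p̄(1−p̄)/n)] / √([p0(1−p0) + p1(1−p1)]/n)}

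ICC 0.23 gives n = 660/8.36 = 78.9. For a 10-point fall:

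- Control 100%: (0.100 − 0.068)/0.0338 = 0.95, so 83%.
- Control 95%: (0.100 − 0.0936)/0.0471 = 0.14, so 55%.

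| Fever, 20 per arm × 33 | 5 points | 10 points | 15 points |
|---|---|---|---|
| ICC 0.05, control 100% | 95% | 100% | 100% |
| ICC 0.23, control 100% | 52% | 83% | 95% |
| ICC 0.05, control 95% | 57% | 97% | 100% |
| ICC 0.23, control 95% | 22% | 55% | 82% |
| Sample-size formula, k = 0.05, control 100% | 77% | 100% | 100% |
| Sample-size formula, k = 0.23, control 100% | 10% | 27% | 54% |

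The k = 0.23 row is probably too low. It adds 0.23² × 1² = 0.0529 of between-cluster variance to a control arm fixed at 100%, which cannot vary. A beta-binomial simulation with a cluster-level paired t-test and control use of exactly 100% gave 59 to 100% at 5 points and about 98 to 100% at 10 points (ICC 0.23 to 0.05).

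For fast breathing (19 per arm × 12), the ICC approximation gives 39 to 74% at a true 15-point rise and 57 to 92% at 19 points (ICC 0.25 to 0.05).

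These are rates for a generic cluster-adjusted test. The Mantel-Haenszel test taken literally, with each cluster as a stratum, has zero numerator and zero variance because each cluster lies wholly in one arm. It supplies no rate of its own.

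**The case against.** The strongest reply is that 20% is simply the design alternative. The objectives ask whether treatment increases and by how much Coartem use falls, section 4.3 powers the trial to show differences, and nothing in the protocol says that p < 0.05 will be reported as confirming 20%. This stands. It makes the fault one of wording and effect measure, not of design. It does not remove the fault, because section 3.2.2 is where the hypotheses are stated and it says something else.

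A second reply is that sections 3.4 and 6.1 work with proportions by arm, so a reader can subtract them. That gives a point estimate but no cluster-adjusted interval. A statistical analysis plan could add one, but here the protocol itself names the effect measure.

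Three stronger readings are tempting and not supported:

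- A reader might infer that significance will usually be reached when the Coartem hypothesis is false, or that almost any share of negative RDTs would suffice. The table shows 10 to 95% at a 5-point fall, depending on assumptions. The highest rates need control use at or very near 100%, and section 4.3 states 100% as what should happen, not as a measured rate.
- A reader might infer that fast breathing is affected as strongly. Its rates are lower and depend heavily on the ICC.
- A reader might count it against the design that, at a true 20-point change, the confidence limit nearest zero reaches 20 points only about 2 to 3% of the time. That holds for any trial whose true effect equals the margin.

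**Conclusion.** The concern holds in limited form. For both endpoints the hypothesis as worded is not what the planned tests examine, so a significant result would establish a change but not one of at least 20 points. This follows from the text and needs no assumption. How often significance would accompany a true change below 20 points is not fixed by the documents. It is frequent for Coartem if control use is close to 100%, and less so with control use at 95% and strong clustering.

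The odds-ratio problem is firm for Coartem at the protocol's own control rate: at 100% it is infinite or not estimable and cannot express the extent of the reduction. For fast breathing the odds ratio is estimable but does not by itself give points. The point is worth correcting before analysis. It does not put the sample size or the trial in doubt.

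**What to change.** - **Section 3.2.2.** Word both hypotheses as superiority: the proportion is higher (early and appropriate treatment) or lower (Coartem use) in the intervention arm. Name 20 percentage points as the difference assumed for the sample size, and write percentage points, since a 20% relative rise from 50% would be 60% and not 70%.
- **Section 6.1.** For each primary outcome, make the risk difference in percentage points with a cluster-adjusted 95% CI the main effect estimate. Keep the odds ratio alongside it where it can be estimated.
- **Interpretation.** Do not describe a significant test as confirming at least 20% unless the confidence limit nearest zero reaches 20 points. This limits the claim. It should not become the success criterion, because the trial was not sized for it.

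The cost is a few lines of text and one more estimate per outcome, with no new sample size. The claim also becomes more modest: an increase or a reduction with its interval, unless the observed change is well above 20 points.
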